### Data analysis

Data will be analyzed according to the 2×2 randomized factorial study designs. The statistical model includes two fixed factors (both local acupoints and distal acupoints). Interaction is evaluated using the interaction term in the ANOVA model and by visual assessment of profile plots. As no interaction between local acupoints and distal acupoints is detected, results are presented as a factorial design (for example, all patients receiving acupuncture at local acupoints in combination with distal non-acupoints; and all patients receiving acupuncture at local non-acupoints in combination with distal acupoints).

Data analysis will be conducted by statisticians who are independent from the research team. Every analysis is conducted using the SPSS software (SPSS 12.0 KO for Windows ©).

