### Randomization and blinding

A research coordinator screen and enroll participants at clinic. After participants completed a baseline evaluation, another research coordinator who is uninvolved with data collection randomly assigns them to one of four treatment groups by using a computer-generated, blocked random-allocation sequence. The random list is generated with SAS software (SAS Institute, Inc., Cary, NC, USA). This research coordinator informs the acupuncturist of the treatment assignment.

The patients, data collection staff, and data analysts are blinded during the study period. The acupuncturist is not blinded to the treatments they delivered because acupuncture manipulation makes it impossible. During the intervention, acupuncturist and the personnel who collect data are segregated immediately after the treatment start and are instructed not to exchange information with each other.

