### Primary outcome measures

Subjective tinnitus loudness and annoyance perception is graded using the VAS. The assessment is at baseline (before treatment initiation), 4 weeks after the first acupuncture session, and 8 weeks after the first acupuncture session.

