### Statistical methods

The trial aims to detect a difference in loudness and annoyance perception of tinnitus between the four study groups. This is deemed a clinically significant difference of average 20-point reduction on the VAS scores of loudness in acupuncture group when comparing with the sham-control group based on previously published studies [14]. The standard deviation is 25.9 in acupuncture group and 23.8 in the sham-control group, respectively, as previous studies have suggested [15].

The following formula was used for a four-group trial [16]:

(1)$$n1=n2=2{\left[\frac{\left(\mathrm{u\alpha}+\mathrm{u\beta}\right)s}{\delta }\right]}^{2}$$

Calculations are performed using 80% power, a 5% significance level (two-side). The required sample size is approximately 24 participants for each group. We plan to enroll a total of 112 participants with 28 in each group, allowing for a 25% withdrawal rate.

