One limitation concerns the fact that this is a single-center study. It does not lend the results to great generalizability to more diverse sets of patients in more diverse settings. Our directed acupuncture treatment is uniformly applied, and adjunctive therapies are not used. In addition, acupuncturists in diverse settings with different philosophies, backgrounds, training, and clinical experiences might have chosen different technique for the directed acupuncture intervention. Therefore, the external validity can be somewhat hard to achieve. But we ensure that the risk of contamination between groups will be minimized, while maintaining the integrity of the experimental group comparison. As a result, whether the findings can be generalized to the clinical setting is unclear and more work is needed.

Another limitation is that the therapist is not blinded in the present trial. A blinded study of acupuncture is challenging to conduct because it is almost impossible to blind acupuncturists to the treatments they are delivering. This study does not allow us to determine whether the observed effectiveness is due to placebo effects, intensity of provider contact, or a physiologic effect of needling. Therefore, a bias due to unblinding cannot be ruled out. In addition, the sample size in the present study is relatively small.

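### The stated factorial ANOVA lists no baseline VAS term, although every patient has a pre-randomisation value; adding it would gain precision at almost no cost

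*Protocol article*

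**What the plan says.** The Data analysis section sets out a 2×2 factorial analysis. "The statistical model includes two fixed factors (both local acupoints and distal acupoints"), and "Interaction is evaluated using the interaction term in the ANOVA model and by visual assessment of profile plots". The listed terms are therefore local, distal and local × distal. No covariate is mentioned.

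Under Primary outcome measures, "Subjective tinnitus loudness and annoyance perception is graded using the VAS", and "The assessment is at baseline (before treatment initiation), 4 weeks after the first acupuncture session, and 8 weeks after the first acupuncture session". THI is scored at the same three times. Under Randomization and blinding, "After participants completed a baseline evaluation, another research coordinator who is uninvolved with data collection randomly assigns them". The baseline value thus exists for every randomised patient and cannot have been affected by treatment.

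The Statistical methods section plans on a "clinically significant difference of average 20-point reduction on the VAS scores of loudness in acupuncture group" compared with sham, with SDs of 25.9 and 23.8, two-sided 5% significance and 80% power. It requires about 24 per group and enrols 28 per group (112 in total) to allow for 25% withdrawal. The section does not say whether the SDs, or the ANOVA response, refer to follow-up scores or to change from baseline. The Discussion concedes that "the sample size in the present study is relatively small".

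**The concern.** A patient's own starting score is usually among the best predictors of the later score on the same scale. The inclusion criteria set no severity range, and randomisation is described as blocked with no mention of stratification, so nothing in the described design balances baseline VAS beyond chance. Leaving it out of the model leaves explainable variation in the error term.

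The precision matters for the question the trial asks. The Discussion wants to know whether local plus distal acupoints do better than either alone. That rests on group A against B and against C, or on the interaction, and these are the contrasts with least power. The interaction result also decides how the findings are presented, so an imprecise interaction test affects the reporting as well as one p-value.

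**Working it through.** **Inputs.** From Statistical methods: difference 20 points; SDs 25.9 and 23.8; two-sided 5%; 80% power; 24 required and 28 enrolled per group; 25% withdrawal. From Data analysis: two factors and their interaction. Assumed, because the documents give no figure: baseline–follow-up correlation r = 0.3, 0.5 or 0.7, and equal variance at baseline and follow-up.

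**Reproducing the plan's figure.** Pooled SD s = √[(25.9² + 23.8²)/2] = √618.6 = 24.87. The plan's formula gives 2 × [(1.960 + 0.842) × 24.87/20]² = 24.28, which matches its approximately 24 per group.

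**Evaluable number.** 28 × 0.75 = 21 per group, below the required 24.

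**Standard errors without baseline, n = 21 per group.**
- Pairwise (one group against another): s√(2/n) = 24.87 × √(2/21) = 7.68
- Interaction, (A − B) − (C − D): 2s/√n = 2 × 24.87/√21 = 10.86
- Main effect (42 against 42): s√(2/42) = 5.43

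Power for 20 points is from the noncentral t distribution. Pairwise power is 72% with two-group error degrees of freedom and 73% with the pooled four-group error. Interaction power is 44%, or 45% by the normal approximation. Main-effect power is about 95%. If all 28 per group are retained, pairwise power is about 84–85%.

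**Reading 1: the SDs are of the follow-up score.** Adding baseline multiplies residual variance by 1 − r², so s becomes 24.87 × √(1 − r²).

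| r | Variance factor | Reduction | Adjusted SD | Pairwise power, n = 21 | Interaction power, n = 21 |
|---|---|---|---|---|---|
| none | 1.00 | – | 24.87 | 72–73% | 44–45% |
| 0.3 | 0.91 | 9% | 23.73 | 76–77% | about 48% |
| 0.5 | 0.75 | 25% | 21.54 | about 84% | about 56% |
| 0.7 | 0.51 | 49% | 17.76 | about 95% | about 72% |

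Pairwise power returns to 80% at about r = 0.4. At r = 0.3 the loss is only partly recovered.

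**Reading 2: the SDs are of change scores.** With σ² the variance of a single score, a change score has variance 2σ²(1 − r) and the ANCOVA residual is σ²(1 − r²). The ratio is (1 + r)/2 = 0.65, 0.75 and 0.85, so variance falls by 35%, 25% and 15%. Replacing s by 24.87 × √[(1 + r)/2] gives pairwise power at 21 per group (pooled error) of about 89%, 84% and 80%, against 73% unadjusted. Compared with reading 1, the gain is larger at r = 0.3, equal at 0.5 and smaller at 0.7.

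**The response becomes immaterial.** Once baseline VAS is a covariate, the estimated treatment effects and their standard errors are the same whether follow-up or change is the response; only the baseline slope shifts by one.

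**The case against.** The strongest reply is that this is a condensed article. It says the model includes two factors, not that it contains nothing else, and covariates are often left to a full protocol or analysis plan that is not shown. This stands in part: a fuller document may already include baseline. But the article does state the model's terms, and a better model is available with data already collected. A covariate added after unblinding would be open to challenge, so it should be settled beforehand.

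A reader might infer three stronger things that the documents do not support:

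- **That the trial ignores baseline.** This is not established. The sample-size target is worded as a reduction, and the secondary outcome for THI is expressed as change. If change is analysed, baseline is used, only less efficiently than by ANCOVA.
- **That the comparison is biased.** It is not. Under randomisation the unadjusted ANOVA is unbiased and its standard error already allows for chance imbalance.
- **That the trial as a whole is short of power and adjustment cures this.** The shortfall applies to pairwise contrasts at 25% withdrawal and to the interaction. It does not apply to a 20-point main effect, nor to pairwise contrasts with full retention. At 21 per group, interaction power stays below 80% even at r = 0.7. The gap between 21 and 24 per group is a separate defect in the withdrawal allowance.

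It is also fair to say that every gain shown depends on an assumed r, and that wide baseline spread is inferred from the entry criteria rather than documented.

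**Conclusion.** The point holds as one of efficiency. The stated model lists no baseline VAS term, and including one would be at least as precise whether follow-up or change is analysed, apart from the single degree of freedom it uses. For r between 0.3 and 0.7 the reduction in residual variance is 9–49% if 24.87 is a follow-up SD and 15–35% if it is a change-score SD. The benefit falls mainly on the pairwise and interaction contrasts that answer the trial's stated question. The main effects have little to gain for a 20-point difference. The size rests on the assumed r, on equal variances at baseline and follow-up, and on the plan's own 25% withdrawal. The change is worth making before the data are unblinded; leaving it out would not invalidate the trial.

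**What to change.** State the response variable and replace the ANOVA with an ANCOVA: VAS loudness at each analysed visit (the article lists weeks 4 and 8 without naming one as primary) on local, distal, local × distal and baseline VAS loudness. Use the same model for VAS annoyance and for THI, each with its own baseline. Record this before unblinding.

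The cost is one sentence in the analysis section and one error degree of freedom (with 21 per group, 84 − 4 = 80 becomes 79). No new data are needed.

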### Interventions

This trial is a randomized, single-blind, controlled study. Participants will receive acupuncture for 4 weeks. All candidates go through a standardized interview and receive more information about the study and the treatments. They also undergo audiological testing of hearing thresholds, minimal masking levels, and loudness discomfort levels carried out by an audiologist in Tongren Hospital affiliated to Capital Medical University.

Time points are as follows (Figure 1):

Visit 1: screening

Visit 2: treatment initiation, participants will receive acupuncture for 4 weeks

Visit 3: 4 weeks after first acupuncture, follow-up and treatment finish

Visit 4: 8 weeks after first acupuncture, follow-up

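### The stated two-factor ANOVA names no baseline or visit term, although the VAS is measured three times and 25% withdrawal is expected; a baseline-adjusted repeated-measures model would be more precise

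*Protocol article*

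**What the plan says.** The Data analysis section calls for a 2×2 factorial analysis: "The statistical model includes two fixed factors (both local acupoints and distal acupoints"). The next sentence adds the interaction: "Interaction is evaluated using the interaction term in the ANOVA model and by visual assessment of profile plots". No covariate, visit term or within-patient correlation is named.

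Under Primary outcome measures, "Subjective tinnitus loudness and annoyance perception is graded using the VAS", and "The assessment is at baseline (before treatment initiation), 4 weeks after the first acupuncture session, and 8 weeks after the first acupuncture session". No visit is singled out as primary. The Interventions section places the end of treatment at the second of these assessments: "Visit 3: 4 weeks after first acupuncture, follow-up and treatment finish".

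The Statistical methods section plans 28 patients per group, 112 in all, "allowing for a 25% withdrawal rate". The article does not say when withdrawals are expected, who forms the analysis set or how missing values are handled.

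**The concern.** A between-patient ANOVA with two factors takes one outcome value per patient. Used as written, it has no place for the baseline VAS, which usually explains part of the variation in later VAS scores, or for a second post-baseline value.

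Two things are at stake:

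- **Precision.** Ignoring baseline widens the confidence interval for each treatment effect, in a trial that the authors themselves call relatively small.
- **Withdrawal.** With a quarter of patients expected to leave, a patient without the analysed value contributes nothing unless it is imputed, even if a week-4 value exists. If patients with little early benefit leave more often from some arms than from others, the effect estimated in those who remain is biased.

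This concerns the model chosen, not missing detail. A later analysis plan that follows the article's wording would inherit it.

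**Working it through.** **Inputs from the article.** SDs are 25.9 and 23.8, the difference is 20 points, alpha is 5% two-sided, power is 80%, and 28 patients per group are enrolled with 25% withdrawal. The root-mean-square SD is √[(25.9² + 23.8²)/2] = 24.87. I take it as the SD of the VAS at a post-baseline visit.

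**The plan's own figure.** n = 2[(1.96 + 0.84) × 24.87/20]² = 24.3 per group, which agrees with the stated 24.

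**Assumed inputs, not in the article.** The baseline/post correlation is 0.5 or 0.6 and the week-4/week-8 correlation 0.7 or 0.8, respectively. The SD is the same at each visit.

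**Step 1: the ANOVA as stated.** After 25% loss, 28 × 0.75 = 21 per group remain, 84 in all. A main effect compares 42 with 42, so SE = 2 × 24.87/√84 = 5.43.

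**Step 2: add baseline.** The SE is multiplied by √(1 − r²).

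| r | Factor | SE | Fall |
|---|---|---|---|
| 0.5 | 0.866 | 4.70 | 13% |
| 0.6 | 0.800 | 4.34 | 20% |

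This gain arises among the patients analysed, so it does not depend on when the others left.

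**Step 3: add week 4 to a week-8 analysis.** Let m be the number of withdrawers per group with a week-4 value (0 to 7), and p the week-4/week-8 correlation given baseline, p = (r48 − r²)/(1 − r²). The SE is multiplied by a further √[1 − p² × m/(21 + m)].

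| r, r48 | p | m = 0 | m = 3.5 | m = 7 |
|---|---|---|---|---|
| 0.5, 0.7 | 0.60 | 0% | 2.6% | 4.6% |
| 0.6, 0.8 | 0.69 | 0% | 3.4% | 6.1% |

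Simulation (28 per arm, random withdrawal, week 4 observed for all) gives SEs of 5.4 to 5.5 for the ANOVA, 4.4 to 4.8 for baseline-adjusted analysis of completers and 4.2 to 4.6 for a likelihood model using both visits. Step 3 is then a gain of about 4% to 7%. If no withdrawer has a week-4 value, the likelihood model has 4.4 to 4.8, the same as baseline adjustment alone.

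**Step 4: bias when withdrawal follows response.** In simulation, patients with a poor week-4 response left the true-local arms preferentially (about 32% lost there against 25% elsewhere). The true main effect was set at 10 points. Mean estimates were:

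| Analysis | Estimate |
|---|---|
| ANOVA in completers | 11.9 |
| Baseline-adjusted, completers | 14.3 |
| Likelihood model, week 4 seen for all withdrawers | 10.0 |
| Likelihood model, week 4 seen for half | about 11.7 |
| Likelihood model, week 4 seen for none | 14.3 |

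The mechanism and the 10-point effect are assumptions. The table shows the direction of the effects and does not forecast their size.

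**The case against.** The strongest reply is that the article is a condensed account. To say that the model includes two factors is not to say that it contains nothing else, and covariates, analysis set and missing-data handling may sit in a fuller document. Much of this stands. A reader might infer that visits are analysed one at a time and that every patient without a value is dropped. The article says neither, and it does not exclude imputation or a change score. What remains is that it names an ANOVA and its terms, and baseline and visit are not among them.

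A change score would not remove the point. Its SE is 5.43 × √[2(1 − r)], which is 5.43 at r = 0.5 and 4.85 at r = 0.6. Baseline adjustment still lowers these by 13% and 11%.

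A reader might also infer that the week-4 value would recover much of what withdrawal costs. The article gives no week-4/week-8 correlation and no dropout timing. Without baseline in the model, and with the correlation varied from 0.3 to 0.9, week 4 restores between 0% and 76% of the lost information on week 8. It restores 11% to 23% at correlations of 0.5 to 0.7 with half the withdrawers seen at week 4. Treatment ends at week 4, so those who leave during treatment may have no week-4 value. If week 4 is itself the primary visit, it cannot fill its own gap.

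The bias argument is open to the charge of circularity: the likelihood model does well when withdrawal depends on data it can see. That stands. Where non-responders leave before week 4, the proposed model reduces to baseline-adjusted analysis of completers, and in Step 4 that was further from the truth than the ANOVA.

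Nor does the point show that main effects lack power. For a full 20-point main effect with 42 per level, power is about 96%.

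**Conclusion.** The point holds as a choice of method that should be improved. The stated model omits baseline and visit despite three planned VAS assessments and 25% expected withdrawal.

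The firm part is baseline: a 13% to 20% smaller SE of a main effect at assumed correlations of 0.5 to 0.6, compared with an ANOVA of the raw score and independent of dropout timing. Using both post-baseline visits adds 0% to about 7%, conditional on quantities the article does not report. Protection against bias is conditional too. It exists only where withdrawal follows a recorded week-4 response, and it rests on data being missing at random.

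The documents do not support saying that the trial will discard patients, that week-4 data will make good most of the loss, or that the proposed model removes withdrawal bias in general.

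**What to change.** Replace the model sentence in the Data analysis section with a mixed model for repeated measures in all randomised patients, by allocated group. The responses are the week-4 and week-8 VAS. The terms are baseline VAS, baseline by visit, visit, local, distal, local by distal, and the interactions of the treatment terms with visit, with an unstructured covariance matrix. Take the treatment contrasts at the primary visit, which has to be named for this purpose.

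State that the analysis assumes missing at random, and add a sensitivity analysis that departs from it. Record for each withdrawal whether it came before or after the week-4 assessment, since the benefit depends on this.

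The cost is a paragraph of analysis text and slightly more programming. Visits, data and sample size do not change. The downside to state openly is the reliance on missing at random: if poor responders leave before week 4, the new model can be more biased than the ANOVA.

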**Discussion:**

Completion of this trial will help to identify whether acupuncture at local acupoints in combination with distal acupoints may be more effective than needling points separately.

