### Aims

The aim of our study is to evaluate the efficacy of acupuncture at local points in combination with distal points in subjective tinnitus patients.

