**Figure 1 F1:**
[figure not shown]
Flowchart.

Patients who meet the inclusion criteria and none of the exclusion criteria are randomized to one of four treatment groups: group A will receive acupuncture at local acupoints in combination with distal acupoints; group B will receive acupuncture at local acupoints in combination with distal non-acupoints; group C will receive acupuncture at local non-acupoints in combination with distal acupoints; group D will receive acupuncture at local non-acupoints in combination with distal non-acupoints. Acupuncture points selected as follows (Figure 2):

 Local acupoints: Baihui (GV 20), Shenting (GV 24), Yifeng (TE 17), Tinghui(GB 2), Ermen (TE 21)

 Distal acupoints: Waiguan (TE 5), Zhongzhu (TE 3), Qiuxu (GB 40), Zulinqi (GB 41)

 Distal non-acupoints

Distal non-acupoint I: the radial side of forearm, the ulner side of the middle of the line joining Shaohai (HT 3) and Shenmen (HT 7), between heart meridian of hand-shaoyin and small intestine meridian of hand-taiyang

Distal non-acupoint II: the radial side of forearm, the junction of the upper 1/4 and lower 3/4 of the line joining HT 3 and HT 7, between heart meridian of hand-shaoyin and small intestine meridian of hand-taiyang

Distal non-acupoint III: lateral side of lower leg, 3 cun above the tip of external malleolus, 1.5 cun behind anterior crest of the tibia, between the stomach meridian of foot-yangming and gall bladder meridian of foot-shaoyang

Distal non-acupoint IV: lateral to the shank, 3 cun below Yanglingquan (GB34), the midway between gall bladder meridian of foot-shaoyang and bladder meridian of foot-taiyang

 Local non-acupoints

Local non-acupoint I: one finger-breadth (middle finger) inferior to Daying (ST5) in the body of mandible

Local non-acupoint II: midpoint between Yangbai (GB14) and the midline of the head, between governor meridian and gall bladder meridian of foot-shaoyang

Local non-acupoint III: high spot of the angle of mandible

Local non-aupoint IV: on zygomatic arch, the midway between ST 7 and GB 3

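### The tests named for the 2×2 ANOVA do not include one of the trial's stated conclusion, that combined acupoints beat local and distal acupoints each used separately

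*Protocol article*

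**What the plan says.** The four groups are the cells of a 2×2 layout (Protocol article, Interventions, text with Figure 1). For the combination, "group A will receive acupuncture at local acupoints in combination with distal acupoints". Group B keeps the local acupoints but has its distal needles at non-acupoints. Group C is the reverse, with true points distally and non-acupoints locally. Group D receives non-acupoints at both sites.

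The Discussion, in the abstract and again in the main text, states the conclusion the trial is to inform: "whether acupuncture at local acupoints in combination with distal acupoints may be more effective than needling points separately". In terms of the groups this is A better than B and A better than C. The Aims are broader: to "evaluate the efficacy of acupuncture at local points in combination with distal points in subjective tinnitus patients". Statistical methods is broader still: "The trial aims to detect a difference in loudness and annoyance perception of tinnitus between the four study groups".

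Data analysis specifies a 2×2 factorial ANOVA with local and distal acupoints as its two fixed factors. On the interaction it says: "Interaction is evaluated using the interaction term in the ANOVA model and by visual assessment of profile plots". It then says that results are presented factorially when no interaction is detected. No path is given for a detected interaction, and the section does not say which result would support the combination claim. Its bracketed illustration of a factorial presentation names groups B and C, which are single cells and not margins.

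**The concern.** Write A, B, C and D for the mean VAS reductions. The conclusion in the Discussion has the null: A is no better than B, or no better than C. The three tests named have other nulls:

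- Interaction: A − B − C + D = 0 (effects add).
- Distal factor: [(A − B) + (C − D)]/2 = 0.
- Local factor: [(A − C) + (B − D)]/2 = 0.

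Each factor effect averages the comparison of interest (A−B or A−C) with one that does not involve the combination (C−D or B−D). A factor effect can be positive because one component beats double sham, even if adding it to the other component does nothing. The factor effects equal A−B and A−C only when the interaction is truly zero, and the plan relies on a test failing to find one. If that test is weak, two significant factor effects do not show that the combination is better. That statement is the trial's headline.

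**Working it through.** **Inputs.** From Statistical methods: difference 20 VAS points (acupuncture against sham control), SDs 25.9 and 23.8, two-sided 5%, 80% power, about 24 required per group, 28 enrolled per group, 25% withdrawal. Assumed: normal VAS changes, equal SDs, and the cell means below. A 25% loss from 28 leaves 21, so results are given for 21, 24 and 28 per group.

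**The plan's own figure.** Pooled SD = √[(25.9² + 23.8²)/2] = 24.87. n = 2[(1.96 + 0.84) × 24.87/20]² = 24.3 per group, which agrees with the stated figure of about 24. This is the size for one cell-against-cell comparison.

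**Standard errors at 24 per group.**
- Interaction: 2 × 24.87/√24 = 10.15.
- Each factor effect: 24.87/√24 = 5.08.
- A−B or A−C: 24.87 × √(2/24) = 7.18.

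**Two opposite truths.**

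*Combination adds nothing:* A=B=C=20, D=0. The interaction is 20 − 20 − 20 + 0 = −20. Each factor effect is (0 + 20)/2 = 10.

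*Only the combination works:* A=20, B=C=D=0. The interaction is +20. Each factor effect is (20 + 0)/2 = 10.

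In both, the interaction is 20/10.15 = 1.97 standard errors from zero and each factor effect is 10/5.08 = 1.97. Each test therefore has about 50% power. The three contrasts are orthogonal, so the chance of no interaction with both factors significant is about 0.5 × 0.5 × 0.5 = 12.5%. Simulation with an estimated pooled variance (200,000 or more trials per case) confirms this:

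| Per group | Truth | No interaction and both factors significant | A>B and A>C both significant |
|---|---|---|---|
| 21 | adds nothing (20/20/20/0) | 11% | 0.5% |
| 24 | adds nothing | 12% | 0.5% |
| 28 | adds nothing | 14% | 0.5% |
| 21 | only combination works (20/0/0/0) | 11% | 60% |
| 24 | only combination works | 12% | 67% |
| 28 | only combination works | 14% | 75% |

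The described path gives the same answer equally often under the two opposite truths. The sign of the interaction would separate them, but the plan gives no rule that uses it. Among trials with no interaction detected, both factors are significant in 24% at 24 per group when the combination adds nothing.

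The joint rule has a false-positive rate of at most 2.5% in favour of A, reached for example when A=B and A is far above C.

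**When effects truly add, 24 per group.**

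| Means A/B/C/D | No interaction and both factors significant | A>B and A>C both significant |
|---|---|---|
| 40/20/20/0 | 90% | 67% |
| 20/10/10/0 | 24% | 14% |

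Power of each contrast alone for a 20-point gap is about 79% at 24 per group. Requiring both lowers it to 67%. By the normal approximation, about 31 evaluable per group would be needed for 80% on the joint rule.

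**The case against.** The strongest defence is that the plan presents factor effects only when no interaction is detected. Under additivity the distal effect equals A−B and the local effect equals A−C, so two positive factor effects do answer the question, and with better power than the joint rule. This stands where effects really add. It does not rescue the plan where they do not, because a 20-point interaction goes undetected about half the time at 24 per group.

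Three stronger readings are tempting and are not supported.

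- A reader might infer that the plan would miss an additive benefit, since the interaction test then rejects only 5% of the time. The protocol uses the interaction to decide on presentation, not as the efficacy test. The described path succeeds in about 90% of trials at 40/20/20/0.
- A reader might take the false-claim rate as 25%, the chance that both factors are significant when the combination adds nothing. That ignores the interaction condition, and the relevant figure is about 12%.
- A reader might say the false claim persists at any sample size. The nulls differ at any size, but the false-claim rate through the described path fades as interaction power grows: 1.9% at 100 per group.

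Two further objections have some force. The wording about needling points separately is in the Discussion and is hedged, while the Aims and Statistical methods are broader. It is nevertheless stated twice as what completion will help to show, and groups B and C fit that question. Also, a separate analysis plan may add cell contrasts. The point here is that the tests the article does name do not match the conclusion it announces.

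**Conclusion.** The point holds in this limited form: the named tests do not have A>B and A>C as their alternative, and at the planned size their described path cannot tell a combination that adds nothing from one that alone works. The size is about 12% under both truths at 24 per group (11% at 21, 14% at 28), against 0.5% and 67% for requiring both contrasts.

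This rests on normal changes, a common SD of 24.87, and assumed cell means. The plan's 20 points is acupuncture against sham control. It is not given for A against B or A against C, and an A−D difference of 40 appears nowhere in the document. It also rests on reading the combination claim from no interaction with both factors significant, because the protocol names no other rule. The matter should be settled before unblinded analysis, and it does not call the design into question.

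**What to change.** In Data analysis, name A−B and A−C on the VAS, estimated from the same four-cell ANOVA, as the test of the combination claim. State that the combination is more effective only if both contrasts favour A at two-sided 5%. No alpha split is needed, because both must succeed. Report the interaction with its confidence interval as a description of synergy or antagonism. Limit the factor effects to statements about local or distal acupoints averaged over the other factor.

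This changes wording only: the data and model stay the same, and the article reports the trial as still recruiting. The cost is power. At 24 per group the joint rule has 67% against 90% for additive 20-point steps, and 14% against 24% for additive 10-point steps. The protocol should therefore give power for the combination claim as about 60% to 75% at 21 to 28 per group for 20-point gaps, and should not carry over the 80% from the single comparison. Reaching 80% would take about 31 evaluable per group, which would be a separate decision on enrolment.
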